**2.13 Proposed type of analysis**

The primary analysis, using a t-test, will be a comparison of mean pre-dialysis systolic blood pressure values from the last month on hemodialysis and the last month on hemofiltration. As described by Zoccali et al, this will give us an assessment of the pressure load as experienced by the left ventricle (92). Supporting analytic and descriptive analysis will be carried out to ensure Consort guidelines can be followed for publication of results.

Continuous outcomes measures for the secondary analysis will be analyzed in exactly the same manner. All efforts will be made to minimize missing values. A sensitivity analysis under extreme but reasonable assumptions will be carried out to evaluate the impact of any missing values.

Lastly, linear regression will be undertaken with systolic pressure as the dependent variable. Treatment type, extracellular fluid volume and sympathetic nervous system activity will be examined for their independent effects on blood pressure control.

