**1.3h DAILY HEMOFILTRATION – Our preliminary pilot data**

Daily hemofiltration has the potential to combine the benefits of both short daily hemodialysis and conventional hemofiltration. However, experience with daily hemofiltration outside of the intensive care unit is limited. We undertook a pilot project using a new system developed by NxStage Medical (Lawrence, MA). The system consists of a simple portable microprocessor controlled cycler for therapy administration and a disposable cartridge for blood and fluid handling (Appendix 1,2). The system is used with pre-packaged solutions much like peritoneal dialysis such that additional plumbing and water requirements are not necessary in the home. Because of the simplicity of the system, patient training time is reduced to approximately 3 weeks.

For the purposes of our prospective pilot study, urea clearance was targeted at 0.40+/-0.5 per treatment 6 days a week in keeping with a standard Kt/V of 2.0. In spite of the lower weekly urea clearance delivered, the patients experienced a reduction blood pressure (Table 1), a 50% reduction in the number of antihypertensive medications, an improvement in quality of life, and in beta-2-microglobulin levels, a marker of middle molecular weight clearance (19,20). However, the study duration was too short to determine if the improvement in blood pressure will be maintained in the long term. In addition, we did not explore the mechanism(s) by which the blood pressure was improved.

Table 1: Improvements in Blood Pressure with Daily Hemofiltration (6x/week) Compared to Conventional Hemodialysis N=7

| Pre Treatment Pressure | Hemodialysis | Hemofiltration | p-value |
| --- | --- | --- | --- |
| Mean Arterial Pressure (mmHg) | 96 (±11) | 86 (±12) | 0.001 |
| Systolic Blood Pressure  (mmHg) | 139 (±18) | 128 (±19) | 0.001 |
| Diastolic Blood Pressure  (mmHg) | 74 (± 9) | 66 (±11) | 0.01 |

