**2.2 Planned trial interventions**

The study will be a 9-month randomized, unblinded, crossover trial of patients comparing short daily (6 days/week) in-centre hemofiltration with a spKt/V (measure of dialysis adequacy: sp=single pool, K= dialyzer clearance of urea, t= time on dialysis, V=volume of urea distribution) of 0.5 (±0.05) to conventional hemodialysis with a spKt/V of 1.2-1.4 yielding approximately equivalent standard Kt/V measurements. A pre and post treatment blood pressure will be measured each treatment, using standard techniques (*see below*). The number, type and strength of antihypertensive medications will be recorded at study entry and at the beginning of each month. Standard laboratory parameters for metabolic control (hemoglobin, calcium, phosphate, albumin, electrolytes, creatinine and urea) will be collected monthly. Additionally, each patient will have an assessment of extracellular fluid volume via bioimpedance, sympathetic nervous system activity via muscle sympathetic nerve activity and ambulatory blood pressure monitoring on 3 separate occasions.

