After the completion of the 3 month hemodialysis run in phase, patients will be randomized to either to a further 3 months of hemodialysis or 3 months of hemofiltration. The starting prescription for hemofiltration will be enough replacement fluid (Hemosol) to achieve a daily (6 days/week) treatment Kt/V of 0.50 (±0.05). Each treatment will take approximately 2-2.5 hours and will occur during the day in centre. Remaining in-centre for the duration of the study avoids the potential bias of typically lower blood pressures at home compared to the clinic environment. The starting prescription for hemodialysis will be unchanged from the preceding 3 months (3 days/week, approximately 3.5-4 hours per treatment). Each patient will undergo measurement of their extracellular fluid volume using bioelectrical impedance, sympathetic nervous system activity using microneurography and ambulatory 24-hour blood pressure measurements (during an off treatment day) prior to the start of and at the end of this 3 month phase. Additionally, each patient will have the standard laboratory investigations repeated on the first Wednesday/Thursday of the month. The nurses will document vitals pre and post each treatment session. Medications, and any adverse events including hospitalizations will be reassessed at the time of monthly blood work.

After completing the 3 months of hemofiltration or hemodialysis, patients will then switch treatment modality for a further 3 months. The same protocol will be followed for laboratory investigations, assessment of vitals, medications and adverse events as during the preceding 3 months. Repeat extracellular fluid volume measurement, muscle sympathetic nerve activity and ambulatory blood pressure recordings will be completed at the end of the study.

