**2.9d SYMPATHETIC NERVE ACTIVITY**

As previously described by the co-applicant (MR), postganglionic multifibre muscle sympathetic nerve activity will be recorded microneurographically using a sterile tungsten microelectrode with a shaft diameter of 200 μm and a non-insulated tip of 5 μm in diameter inserted into a muscle fascicle of the peroneal nerve posterior to the fibular head. A reference electrode is inserted subcutaneously 1 – 2 cm from the recording electrode. Electrodes will be connected to the remote, low noise preamplifier of the Nerve Traffic Analyzer, (University of Iowa, Iowa City, Iowa). The neural signal will be amplified by 40,000, input to a bandpass filter (0.5 to 1 KHz) and integrated to obtain a mean voltage neurogram. The mean voltage neurogram, ECG, respirations and BP signals will be digitized with a sampling frequency of 2,000 to 5,000 Hz, and recorded on a Ponemah Data Acquisition System (Gould, Valley View, OH). Pulse synchronicity and low signal-to-noise ratio will confirm burst activity as being of muscle sympathetic efferent origin. MSNA (burst/min and bursts/100 beats) will be calculated from 10-minute recordings after 20 minutes of rest. Muscle sympathetic nerve activity recordings will be performed at the time of randomization, after the first 3 months of the cross-over phase and again at study completion when the patient is at their dry weight.

**2.10 What is the proposed sample size?** 20 patients. Based on our previous pilot study, assuming a standard deviation of 11, an alpha = 0.05, we will have 80% power to detect a difference of 11 between the groups.

**2.11 Planned recruitment rate –** Patients will be recruited from the ~ 600 patients undergoing in-centre hemodialysis at the Ottawa Hospital. Due to limited access to the machines for hemofiltration a maximum of 10 patients can be treated in each 6 month period. Allowing for upfront recruitment and training time, it is anticipated that it will take 18 months to recruit all of the patients with a further six months after the last patient is recruited to complete the study. Data analysis and manuscript preparation are expected to take an additional 6 months.

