**2.14 Feasibility**

In a review of our hemodialysis program, 85 patients were identified who fulfilled criteria for resistant hypertension (3 or more drugs on 3 consecutive runs, blood pressure >140/90). Assuming that 50% of patients would be potentially interested in participating in the study, we will have enough study candidates. However, we are concerned that patients may not want to return to hemodialysis after daily hemofiltration and have therefore limited the study duration to 9 months. Patients will also have the opportunity to select the modality of their choice as their long-term treatment option upon completion of the study. Lastly, we have Health Canada approval to use Normocarb for this study but have sent in an amendment to be able to use Hemosol as this solution is available in larger bags and comes premixed decreasing the nursing workload.

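### The primary test of this two-period crossover is named only as a t-test: it is not stated to be within patient, has no period term, and is not limited to the randomized phase

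*Protocol*

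**What the plan says.** Section 2.2 describes a "9-month randomized, unblinded, crossover trial of patients". Under Section 2.9, patients spend three months on hemodialysis as a run-in and are then randomized to three months of either modality, after which "patients will then switch treatment modality for a further 3 months". Section 2.13 gives the analysis: "The primary analysis, using a t-test, will be a comparison of mean pre-dialysis systolic blood pressure values from the last month on hemodialysis". The other side of the comparison is the corresponding month on hemofiltration. Continuous secondary outcomes are to be handled identically. No pairing, period or sequence term is mentioned, and nothing says which hemodialysis months qualify.

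Section 2.10 gives the sample size as "20 patients. Based on our previous pilot study". Its stated inputs are "assuming a standard deviation of 11, an alpha = 0.05", and its claim is "80% power to detect a difference of 11 between the groups". It does not say whether the SD belongs to a single measurement or to the within-patient difference. Section 2.14 adds that "we are concerned that patients may not want to return to hemodialysis after daily hemofiltration".

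**The concern.** A crossover earns its efficiency by comparing each patient with himself or herself. Section 2.13 does not claim that comparison, and the wording of Section 2.10 belongs to a parallel-group trial, so an analyst could run a two-sample test and follow the text.

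The other reading, a paired t-test, still ignores period. Dry weight and antihypertensive drugs are being changed during the run-in, and medications are reassessed monthly afterwards, so a shift in blood pressure between the two randomized periods is plausible. Whether such a shift reaches the treatment estimate depends on the balance of the two sequences. Section 2.9 gives no allocation ratio or blocking, and the dropout feared in Section 2.14 would fall on one sequence.

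Finally, the run-in is also hemodialysis. Nothing in Section 2.13 stops a run-in month from standing in for a missing randomized hemodialysis month. At stake are the power and error rate of the primary test, its freedom from period bias, and the randomized basis of each patient's comparison.

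**Working it through.** **Inputs.** From Section 2.10: n = 20, difference 11 mmHg, SD 11, alpha 0.05 (taken as two-sided, since the text does not say). From Section 2.12: 2 expected dropouts, leaving 18. From the pilot table in Section 1.3h (N = 7): systolic pressure "139 (±18) | 128 (±19) | 0.001", so an SD of about 18.5. The within-patient correlation ρ is not given; it is assumed, and a range is shown.

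**1. The plan's own figure.**
- Two parallel arms of 10: power 56%. Does not reproduce.
- Paired, with 11 as the SD of the difference, n = 20: power 98.9%. Does not reproduce.
- Paired, with 11 per measurement and ρ = 0: SD of difference = 11√2 = 15.56; 18 patients give 80.7%, and 18/(1 − 0.10) = 20. Reproduces.

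The stated size therefore fits a calculation in which every patient contributes to both conditions but no credit is taken for within-patient correlation. The document does not say that this was the calculation.

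**2. Unpaired against paired.** With per-measurement SD s, the standard error used by the unpaired test is s√(2/n), whatever ρ is. The paired one is s√(2(1 − ρ)/n). For n = 18 and ρ = 0.5 these are 3.67 and 2.59 at s = 11, and 6.17 and 4.36 at s = 18.5. Simulated results for effect 11:

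| ρ (assumed) | s = 11: unpaired / paired power | s = 18.5: unpaired / paired power | Type I error, unpaired |
| --- | --- | --- | --- |
| 0 | 83% / 81% | 41% / 39% | 0.05 |
| 0.3 | 87% / 92% | 39% / 52% | 0.02 |
| 0.5 | 90% / 98% | 38% / 66% | 0.008 |
| 0.7 | 94% / >99% | 36% / 87% | 0.001 |

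The pilot shows the same contrast. Unpaired, its systolic row gives t = 11/√((18² + 19²)/7) = 1.11 on 12 df, p = 0.29, against the reported 0.001. If that 0.001 came from a paired t-test (an assumption), t on 6 df is 5.96, the SD of the difference is 11√7/5.96 = 4.9, and ρ is about 0.97.

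**3. Paired without period.** Let π be the difference between periods. It shifts the within-patient difference by +π in one sequence and −π in the other, so the bias is π(n₁ − n₂)/(n₁ + n₂):
- 10:10: 0
- 11:9: 0.10π
- 12:8: 0.20π

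The sign depends on the direction of drift and on which sequence is larger. With π = 5 at 12:8, a true effect of 11 is estimated as 10 or 12. Under simple 1:1 randomization of 20 patients, 12:8 or worse has probability 0.50.

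With equal sequences, π enters the variance instead. For SD of difference 11 and π = 8, the apparent SD is about √(11² + 8² × 20/19) = 13.7. At effect 11, power is 96% without a period term and 99% with it. At 12:8 with π = 5 in the unfavourable direction, it is 95% against about 99%. The values of π are illustrative, as the document gives none.

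**4. Which month is the last hemodialysis month?**
- Hemodialysis first, completer: month 6, randomized.
- Hemofiltration first, completer: month 9, randomized.
- Hemofiltration first, never starts the hemodialysis period: month 3, the run-in, if the words are applied literally.

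**The case against.** The strongest reply is that the text is silent on pairing and does not specify an unpaired test. In a crossover a paired t-test is the natural reading, and a t-test on within-patient differences compared by sequence is also a t-test and removes period. A statistical analysis plan, not shown here, could settle this. That stands against any claim that the plan prescribes an unpaired test. It does not fully answer the point, because Section 2.13 does fix a named method, fixes the two quantities compared and extends the method to the secondary outcomes. A t-test applied directly to those quantities, paired or unpaired, does not use period.

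A reader might infer that most of the power is wasted. On the plan's SD of 11 that is wrong: unpaired power stays above 80% at every correlation shown. A large loss needs the pilot systolic SD and substantial correlation. At that SD and ρ = 0.5 even the paired test reaches only 66%, so part of the shortfall belongs to the SD assumption, which is a separate matter.

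A reader might also infer that drift necessarily biases the result, or that run-in data enter routinely. With equal sequences the bias is zero, and two dropouts may leave 9:9. No completer contributes run-in data, and no text says a dropout would be paired with them. Section 2.14 says the study was kept to 9 months because of this worry, and Section 2.13 plans a sensitivity analysis for missing values. Those points limit the exposure but leave the wording open.

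**Conclusion.** The point holds as a defect of specification with bounded consequences. The primary analysis, as fixed, is not tied to a within-patient, period-adjusted comparison confined to randomized data.

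- **If run unpaired:** the test is conservative whenever ρ is positive. The power cost at the stated SD is nil at ρ = 0 and about 8 points at ρ = 0.5. At an SD of 18.5 it is about 28 points at ρ = 0.5 (38% against 66%) and about 51 at ρ = 0.7 (36% against 87%). These figures rest on assumed correlations and 18 completers.
- **If run paired without period:** bias is 10% to 20% of the period difference at 11:9 to 12:8 splits, in either direction. With balanced sequences there is a modest loss of precision and no bias.
- **Run-in data:** the risk is confined to hemofiltration-first patients who do not begin hemodialysis, the kind of dropout the investigators themselves say they fear.

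The documents do not support saying that the plan chose an unpaired test, that it forfeits most of its power, or that the estimate is certain to be biased.

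**What to change.** In Section 2.13, state that the primary analysis is a within-patient comparison with treatment and period effects. Either of two forms would do:
- a period-adjusted crossover t-test on within-patient differences by sequence; or
- a linear mixed model with fixed treatment and period effects and a random patient effect, which also keeps patients with one period.

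Define both outcome months as month 3 of the respective randomized period, and state that run-in hemodialysis is never used as the hemodialysis period. Apply the same analysis to the continuous secondary outcomes. In Section 2.10, replace the parallel-group wording and say whether the SD of 11 is per measurement or of the within-patient difference.

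The cost is wording and one degree of freedom. With 20 patients, effect 11, per-measurement SD 11 and ρ = 0, adding the period term moves power from 85.1% to 84.8% when there is no drift.

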**2.14 Feasibility**

In a review of our hemodialysis program, 85 patients were identified who fulfilled criteria for resistant hypertension (3 or more drugs on 3 consecutive runs, blood pressure >140/90). Assuming that 50% of patients would be potentially interested in participating in the study, we will have enough study candidates. However, we are concerned that patients may not want to return to hemodialysis after daily hemofiltration and have therefore limited the study duration to 9 months. Patients will also have the opportunity to select the modality of their choice as their long-term treatment option upon completion of the study. Lastly, we have Health Canada approval to use Normocarb for this study but have sent in an amendment to be able to use Hemosol as this solution is available in larger bags and comes premixed decreasing the nursing workload.

